#### Exclusion criteria

We will exclude caregivers of patients who are terminally ill, discharged to alternative levels of care, or discharged to long-term care or assisted retirement residences.

### Interventions

Participants in intervention arms 1 and 2 will receive the TIRSFSP Guide. This educational resource contains an introductory chapter, one chapter for each phase in the TIR framework, and a concluding chapter containing lists of local resources available to the patient and caregiver (see Table 1). The content of each chapter is based on the TIR framework [16] and caregivers descriptions of their phase-specific experiences and needs obtained during a previous qualitative study [15]. We leveraged existing educational and support resources, created new resources, and organized them according to the phases of the TIR framework. Each chapter provides emotional support by describing how some caregivers may feel emotionally during each phase [15]. Each chapter also provides a “who to talk to for help” section to guide caregivers as to who they should speak with for certain areas of concern (e.g., speech language pathologist to learn more about communicating with a stroke survivor with aphasia). The introduction to the guide instructs caregivers to “self-manage” their support needs [42,43]. It provides caregivers with strategies for eliciting help and support from family and friends, communicating effectively with health care professionals, obtaining community services, and succeeding at caregiving. Caregivers will be instructed to review the information in each chapter as it becomes relevant to their current situation (i.e., as they move through the TIR phases). Caregivers can review the guide as often as they like.

1. Stroke Support Person TIRSFSP: The intervention will be delivered by a stroke support person in-person during the acute care phase and then by monthly telephone calls for approximately six months after the stroke survivor is discharge home. The stroke support person is a health care professional involved in the coordination of stroke services and provision of education and support (e.g., occupational therapist, social worker, nurse educator, case manager). During each session, the stroke support person will ask caregivers how things have been going, how they are doing, and what their needs are so they can guide them through appropriate sections of the TIRSFSP educational resource and help them obtain the supports they currently need. The stroke support person will encourage, using self-management principles, caregivers to obtain the needed supports from the appropriate health care professional (e.g., training in caregiving activities from an occupational therapist) or appropriate community resources. They will give the caregivers a copy of the TIRSFSP guide as a resource. The support person will encourage the caregiver to contact them between regular appointments if they have any specific questions. Our pilot study indicated that the first meeting is the longest and takes approximately 60 minutes and subsequent meetings are 10–30 minutes each [44]. The intervention content and duration, including time spent during each session and number of sessions, is tailored to individual caregivers’ experiences and needs.

2. Self-Directed TIRSFSP: In the second arm of this trial, family caregivers will self-direct their use of the TIRSFSP guide. The stroke support person will meet with the caregiver once during the acute stroke phase to instruct them on the use of the guide. They will provide an overview of the self-management principles and encourage them to manage their support needs.

3. Standard Care: Current standard care in the stroke centres of the Ontario Stroke System is for stroke survivors and/or family members to receive a copy of the Heart and Stroke Foundation’s “Let’s Talk about Stroke” educational resource. This resource provides general information that is not specific to phase of recovery, to educate stroke families about what a stroke is, treatment options, secondary prevention, and impact on stroke survivors’ health and well-being. The research assistant will ensure that all caregivers recruited into the trial receive a copy of “Let’s Talk about Stroke” with a brief introduction to its contents.

**Table 1 T1:** Contents of the timing it right stroke family support program guide

**Chapter**	**Title**
1.	Introduction to the program
2.	My family member has had a stroke
3.	My family member’s condition has stabilized
4.	My family member is preparing to go home
5.	My family member has just returned home
6.	Adapting to life in the community
7.	Additional resources

### Data collection

Three sources of data will be collected in the form of structured quantitative measurement instruments, qualitative interviews, and stroke support person journals.

Structured Quantitative Measurement Instruments: Caregiver outcomes are the focus of this study. The research assistant in each region will obtain the baseline and follow-up data at 3, 6, and 12-months post-stroke. All measurement instruments have been used previously in stroke caregiving research and demonstrate good psychometric properties [45-47]. In the pilot study, administration of these quantitative measures took approximately 30–45 minutes [44]. All data will be entered into the EmPower web-based system that will support and manage the data this clinical trial [48]. Caregivers will be able to complete mailed surveys or enter their responses directly into EmPower.

The primary outcome, caregiver’s perceived social support, will be assessed by the Medical Outcomes Study Social Support Scale [49]. Positive and negative mental health outcomes, will be assessed by the Positive Affect Scale [50] and the Centre for Epidemiological Studies Depression Scale [51], respectively. Caregivers’ participation in valued activities, will be assessed by the Caregiving Impact Scale [45,52]. The level of assistance provided to the stroke survivor in terms of activities of daily living, instrumental activities and medical care will be assessed by the Caregiving Assistance Scale [45,52]. Caregivers’ stroke knowledge concerning warning signs, causes, consequences, treatment options, rehabilitation, and secondary prevention will be assessed by the Stroke Knowledge Test [53]. Caregivers’ sense of control over life will be assessed by Pearlin’s Mastery Scale [54]. Personal development as a result of providing care will be assessed by Pearlin’s Personal Gain Scale [55]. To facilitate an economic analysis related to the intervention, we will also collect Health Resource Utilization data (adapted from Brown, 1990 [56]. Sociodemographic characteristics of the caregiver will also be assessed. Stroke patients’ charts will be reviewed to obtain the following information: stroke severity (Canadian Neurological Scale [57] completed during the first week of hospital admission), functional status as measured by the Barthel Index [58], stroke type and location, and date of stroke.

#### Qualitative interviews

A sub-sample of 36 (12 per intervention arm) caregivers will participate in a qualitative interview after the completion of the final follow-up assessment. Research assistants with training in qualitative interviewing will conduct all the interviews by telephone. Telephone interviews have been shown to provide qualitative data of the same quality and quantity as in-person interviews [59]. We will use framework methodology to describe caregivers’ experiences and needs during each phase of the TIR framework and how the intervention arm that they received did or did not meet their needs [60,61]. Based upon our pilot study, we estimate the qualitative interviews will take approximately 45–60 minutes [44].

#### Stroke support person journals

For each site, the stroke support person will complete a journal to record the details of the intervention provided to participants. Specifically, for each contact with each caregiver, they will record the duration of the contact, topics discussed, and resources provided. This information will help us to understand more fully the role that the stroke support person fills and the time commitment to fill this role.

### Sample size

The target sample size is 300 family caregivers (see Figure 2). With a sample of 100 participants per group we will be able to observe a medium sized difference between three treatment groups in our primary outcome, caregiver’s perceived social support (Social Support Survey, mean 73.3, SD 20.8) (80% power, P < .05 significance) [62]. The estimated sample size remained the same when calculated using the Center for Epidemiological Studies - Depression Score and the Positive Affect Scale as outcome measures (described above). Our sample will include caregivers from urban (n = 240) and rural (n = 60) environments to be representative of the Canadian population (approximately 80% urban and 20% rural). We are using Statistics Canada’s rural definition “A community (generally a municipality in the west and a township in the east) is defined as “rural” if its population density is less than 150 people per square kilometer”.

**Figure 2 F2:**
[figure not shown]
Anticipated CONSORT diagram including follow-up protocol and qualitative data collection.

A sub-set of 36 family caregivers will participate in the qualitative portion of the study. Based on our previous qualitative study with stroke family caregivers, we are confident that this number will ensure saturation of research themes [15,63]. Caregivers will be purposively sampled to reflect the intervention groups (i.e., 12 participants per research group) [64].

### Randomization

Research assistants responsible for recruiting participants into the study will enter baseline data into EmPower and EmPower will use a random number generator to place participants into one of the 3 treatment arms: A) TIRSFSP delivered by a stroke support person, B) TIRSFSP self-directed by the caregiver, and C) standard care. EmPower will email the stroke support person to inform them when a participant has been randomized. We will use stratified randomization to ensure an equal distribution of participants across intervention arms within each site.

### Blinding

The research assistant who collects the baseline and follow-up data will be blind to group assignment.

### Statistical methods

#### Analysis of quantitative data

We will analyze the data on the principle of intention to treat. Hierarchical linear modeling for longitudinal data will examine changes in caregiver outcomes over the follow-up period and examine differences between study groups for each outcome [65]. We will use mixed effects modeling as it accounts for the underlying heterogeneity between and within participants (i.e., intercepts and slopes are allowed to vary across participants). This approach will also allow us to identify differences in rates of change (slopes) in the dependent variables between study groups (e.g., participants in the intervention group with a support person may have earlier improvements in stroke-related knowledge). It will also allow us to control for confounding variables that can also influence caregiver outcomes (e.g., stroke severity). Because intercepts and slopes are computed for each participant, caregivers who miss a follow-up assessment or drop out of the study are still included in the data analyses.

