## Methods

### Trial design

We will conduct a convergent parallel mixed methodology [41], longitudinal, multi-site, single-blind randomized controlled trial. As a convergent parallel mixed methodology design, the quantitative and qualitative portions of the study will provide different but complementary perspectives on caregivers’ experiences with support received [41]. Recruitment will take place in 7 acute care hospitals from across Canada. Caregivers will be recruited during the patients’ acute care hospital admission. They will complete baseline assessments prior to randomization and follow-up assessments at 3, 6, and 12-month’s post stroke. All caregivers will provide written informed consent. The research protocol has been approved by institutional research ethics boards at all participating hospitals, including the following: University Health Network Research Ethics Board, Capital Health Research Ethics Board, Ottawa Hospital Research Ethics Board, University of Toronto Office of Research Ethics, University of Calgary Faculty of Medicine Office of Medical Bioethics Conjoint Health Research Ethics Board, Pembroke Regional Hospital Research Ethics Committee, Thunder Bay Regional Health Sciences Centre Research Ethics Board, Lakeridge Health Research Ethics Board, Queen’s University Health Sciences & Affiliated Teaching Hospitals Research Ethics Board, Health PEI Research Ethics Board, Royal Victoria Hospital Research Ethics Board, and Cape Breton District Health Authority Research Ethics Board.

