#### Analysis of stroke support persons’ journals

The stroke support persons’ journals for each phase will be reviewed to determine: 1) the amount of time the stroke support person spends with each caregiver, 2) the topics discussed, and 3) the resources provided. This information will be summarized for each site’s stroke support person and then averaged across sites. The topics and resources provided will be synthesized using conventional content analysis [67,68]. Specifically, for each phase of the intervention, we will count the number of times each topic is discussed and each resource is provided to identify the key topics and resources for each phase of the intervention.

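### The stated model names neither site, the randomisation stratum, nor support-person variation, so its standard errors may be off in a direction that depends on unknown variance shares

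*Protocol article*

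**What the plan says.** Protocol article, Trial design: "Recruitment will take place in 7 acute care hospitals from across Canada".

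Randomization: "We will use stratified randomization to ensure an equal distribution of participants across intervention arms within each site".

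Interventions, arm 1: "The intervention will be delivered by a stroke support person in-person during the acute care phase and then by monthly telephone calls". Arm 2: "The stroke support person will meet with the caregiver once during the acute stroke phase to instruct them on the use of the guide". Standard care has no session with that person.

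Stroke support person journals: "For each site, the stroke support person will complete a journal to record the details of the intervention provided to participants". The section on analysing the journals is again in the singular: "This information will be summarized for each site’s stroke support person and then averaged across sites". The article does not state one person per site as a rule, but both passages read that way.

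Analysis of quantitative data: hierarchical linear (mixed effects) modelling is chosen because "it accounts for the underlying heterogeneity between and within participants (i.e., intercepts and slopes are allowed to vary across participants". The section adds that the model can adjust for confounders, with stroke severity as the example. Site and stroke support person are not mentioned.

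**The concern.** Two features of the design produce correlation that the described model does not represent.

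The first is the stratum. Arms are balanced within site, so differences in outcome level between sites cancel from the arm contrasts. A model without site leaves those differences in the error term, which makes its standard errors for level contrasts too large. The reference to confounders does not obviously bring site in, because a factor balanced by design is not a confounder. It belongs in the model because the randomisation was restricted on it.

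The second is the provider. If one person per site delivers arm 1 through repeated contact, arm 1 caregivers at a site share that person's effect and standard care caregivers do not. The effect appears as site-by-arm variation and does not cancel from the contrast. Omitting it makes standard errors too small. Hypothesis 2 rests wholly on arm 1 contrasts and Hypothesis 1 partly. Arm 2, with a single meeting, would be affected less.

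**Working it through.** **Inputs from the article.** 100 caregivers per arm; 7 hospitals; Social Support Survey SD 20.8; 80% power; P < .05 (two-sided assumed). Trial design also lists 12 ethics boards, which need not match recruiting hospitals one to one, so 12 sites serves as a sensitivity value.

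**Assumptions.** The article gives no intraclass correlation for site or support person. Variance shares from 0.02 to 0.10 are assumed below.

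**The plan's own figure.** The target of 100 per group is for a medium difference that is given no number. A pairwise standardised difference of 0.4 (0.4 × 20.8 = 8.3 points) needs 99 per group, and 100 gives 80.7% power. A difference of 0.5 needs only 63. The stated size therefore fits 0.4, but only if that value is assumed. No clustering allowance is stated.

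**(a) Shared site effect omitted.** For a comparison at one time point, model SE / true SE ≈ 1/√(1 − ICC): 1.026 at 0.05 and 1.054 at 0.10. Simulation (20,000 runs, 7 sites) gives 1.023 and 1.041, with type I error .044 and .041. With site as a fixed effect it returns to .049 and .051. A site difference that is constant over time is largely absorbed by the participant intercepts when slopes are compared, so this part has little bearing on slope contrasts.

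**(b) Support-person variation in arm 1 omitted, arm 1 versus standard care.** Let r be the support-person share and K the number of sites. With total variance scaled to 1:

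- true variance = (1 − r)/100 + r/K + 1/100
- model variance = 2/100
- K = 7, r = 0.02: 0.0098 + 0.00286 + 0.01 = 0.02266; SE ratio √(0.02266/0.02) = 1.064; type I error 2 × [1 − Φ(1.96/1.064)] = .066
- K = 7, r = 0.05: 0.0095 + 0.00714 + 0.01 = 0.02664; ratio 1.154; type I error .090
- K = 12, r = 0.02 and 0.05: ratios 1.036 and 1.088; type I error .059 and .072

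With 7 sites and a standardised difference of 0.4, power using the true standard error falls from .807 to .757 and .688.

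**(c) Both present (simulated type I error, arm 1 versus standard care).**

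| Sites | Site share | Support-person share | Site omitted | Site as fixed effect |
|---|---|---|---|---|
| 7 | 0.05 | 0.02 | .062 | .068 |
| 7 | 0.10 | 0.02 | .056 | .069 |
| 7 | 0.05 | 0.05 | .081 | .091 |
| 12 | 0.05 | 0.02 | .051 | .058 |
| 12 | 0.10 | 0.02 | .047 | .059 |
| 12 | 0.05 | 0.05 | .067 | .076 |

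The errors offset in part, and less so as the support-person share grows. A site fixed effect removes the conservative component and leaves the provider component in place. With support-person variation alone and 7 sites, type I error under site fixed effects is about .064 at r = 0.02 and .093 at r = 0.05.

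**The case against.** The strongest objection is that this is a condensed article and the full list of model terms normally sits in the analysis plan, which is not shown. The sentence on heterogeneity explains why mixed models were chosen and is not a closed specification. Hierarchical modelling can take a site level, and the covariate list is open. This stands as far as it goes: a reader might infer that the model excludes site or contains only participant-level variation, and the text does not say so. But the section is not silent either. It spells out which effects vary, and that description does not reflect the stratified, provider-delivered design set out elsewhere in the article.

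A reader might also infer that the standard errors are wrong, or that false positives are inflated. Neither is shown. No variance shares are given, the two omissions act in opposite directions, and if both shares are near zero the standard errors are essentially right. The site part is small and conservative.

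Two further points stand. One support person per site is inferred from singular wording. And the number of clusters is not certain, which is why results for 12 sites are given beside those for 7.

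**Conclusion.** The point holds in a limited form. As described, the model names neither the randomisation stratum nor support-person variation, and fitting it that way could misstate the uncertainty of the arm contrasts. The provider part matters more: at assumed shares of 0.02 to 0.05 it takes type I error for arm 1 versus standard care to about .066 to .090 with 7 sites, while the site part on its own takes it to about .044 to .041. With both present the computed values run from .047 to .062 at a support-person share of 0.02, and are .067 (12 sites) and .081 (7 sites) at 0.05.

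These figures rest on assumed variance shares, equal numbers per site, one support person per site, no provider effect in standard care, and a comparison at a single time point. They show the plausible scale and sign of the error and do not predict it for this trial. The change is worth making because it is nearly free and because any offset between the two omissions would be accidental.

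**What to change.** 1. State that site, as the randomisation stratum, enters every primary and secondary outcome model as a fixed effect. With 7 sites this uses 7 − 1 = 6 degrees of freedom.
2. Prespecify one sensitivity analysis with a random site-by-arm (support-person) term for the contrasts involving arm 1. The first change does not do this job: with one person per site, the provider effect in arm 1 is site-by-arm variation, which a site main effect cannot remove.
3. Say in advance that about 7 clusters estimate this variance imprecisely. The analysis is therefore a check on the arm 1 conclusions, and an estimate near zero would not prove that support persons are interchangeable.

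The cost is a few degrees of freedom, one extra analysis and a short addition to the analysis section. Site is known from randomisation and contacts are logged in the support persons' journals, so no new data are needed.

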#### Analysis of qualitative data

The in-depth qualitative interviews will be analyzed using the 5 stages of framework analysis: 1) familiarizing by listening to the interviews and reviewing the transcripts; 2) selecting a thematic framework (e.g. TIR model); 3) indexing or coding the data according to the framework; 4) charting the data on the framework, and 5) interpretation [60,61]. This approach will allow examination of caregivers’ changing experiences and needs across the recovery trajectory and determine the extent to which their arm of the intervention met their needs. With this number of qualitative interviews (e.g., 12 participants per intervention arm) we will be able to compare and contrast caregivers’ experiences and needs across intervention arms. Researcher bias is a common threat to the trustworthiness of qualitative data analysis. To minimize this threat we will use the following strategies as recommended by McReynolds [64]: 1) we will maintain an audit trail by keeping record of all data, analysis procedures, and analysis notes; 2) multiple researchers will contribute to the data analysis and theme generation; and 3) we will carefully examine discrepant data (i.e., data that does not support the researchers preliminary conclusions) [64]. We will use NVivo 10 qualitative software to organize the coding process [66].

#### Analysis of stroke support persons’ journals

The stroke support persons’ journals for each phase will be reviewed to determine: 1) the amount of time the stroke support person spends with each caregiver, 2) the topics discussed, and 3) the resources provided. This information will be summarized for each site’s stroke support person and then averaged across sites. The topics and resources provided will be synthesized using conventional content analysis [67,68]. Specifically, for each phase of the intervention, we will count the number of times each topic is discussed and each resource is provided to identify the key topics and resources for each phase of the intervention.

